### Eligibility criteria

Patients must satisfy all of the following inclusion criteria. The inclusion criteria are as follows: (1) symptoms of diarrhea or constipation; (2) three or higher in Gastrointestinal Symptom Rating Scale (GSRS) subdomain score (diarrhea or constipation); (3) T2DM patients without diabetic polyneuropathy; (4) no new antibiotic usage within 12 weeks prior to consent; (5) no new diet interventions within 12 weeks prior to consent; (6) no changes in medications which can affect gastrointestinal symptoms and microbiome (addition or discontinuation of medications or change in use or dosage of medications) within 12 weeks prior to consent; (7) aged 20 and up and under 75 years or less at the time of consent; (8) written consent obtained from the individual. The exclusion criteria are as follows: patients with (1) mean defecation frequency < 1 or > 42 times/ week within 4 weeks before giving their consent; (2) structural diseases, including inflammatory diseases (infectious enteritis, diverticulitis, Crohn’s disease, and ulcerative colitis), and stenotic lesions, diagnosed by colonoscopy within 5 years before giving their consent; (3) having both ≥ 3 on the GSRS constipation subscale and > 4 on the Bristol stool scale; (4) having both ≥ 3 on the GSRS diarrhea subscale and < 4 on the Bristol stool scale; (5) gastrointestinal symptoms of both diarrhea and constipation; (6) past history of inflammatory bowel disease and celiac disease; (7) HbA1c level ≥ 9% at the time of consent; (8) use of alpha-glucosidase inhibitors within 4 weeks prior to consent; (9) cerebral infarction, stroke, or myocardial infarction within 12 weeks prior to consent; (10) severe hepatic dysfunction defined as alanine aminotransferase (ALT) or aspartate transaminase (AST) level 5 times equal or higher than the upper normal limit; (11) severe renal dysfunction defined as estimated glomerular filtration rate < 30 mL/min/1.73 m^2^; (12) active malignant tumor; (13) allergy history of bifidobacteria; (14) usage of any other supplements or medications that affect intestinal function; (15) usage of medications that are likely to cause abdominal symptoms (e.g., gastroprokinetic agents, drugs for dyspepsia, antiemetic agents, laxatives, and anticholinergics); (16) patients with changes in diet within 12 weeks prior to consent; (17) other conditions that the researcher or investigator thinks inappropriate for the study.

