#### Outcomes

The primary endpoint of this trial will be the change in the total GSRS score from baseline to follow-up examination (12 ± 3 weeks after baseline examination). Secondary endpoints of this trial will be as follows: (1) change and percent change in following parameters from baseline to follow-up examination: GSRS subdomain scores, fecal properties/Bristol stool form scale, defecation frequency, blood test biomarkers (total bile acid, glycoalbumin, glucagon-like peptide-1, glucose-dependent insulinotropic polypeptide, glucagon, HbA1c, fasting plasma glucose, C-peptide, AST, ALT, gamma-glutamyltransferase, total cholesterol, high-density lipoprotein cholesterol, low-density lipoprotein cholesterol, triglycerides, blood urea nitrogen, and creatinine), physical examination (body weight and body mass index), urinary albumin creatinine ratio, gut microbiota (type of enterobacteria, relative abundance, alpha diversity, and beta diversity), macronutrients (total energy, carbohydrate, fat, protein, and dietary fiber intakes measured by brief-type self-administered diet history questionnaire [BDHQ]) [16]; (2) proportion of participants whose fecal property of Bristol stool form scale is within normal range (3.5–4.5); (3) medication adherence to the BBG9-1; (4) factors that affect GSRS total score or constipation/diarrhea subdomain scores; (5) stratification of following items by baseline symptoms (constipation/diarrhea): GSRS total score, GSRS subdomain scores, proportion of participants whose fecal properties are within normal range, defecation frequency, blood test biomarkers, and gut microbiota. The exploratory endpoints of this trial will be as follows: (1) blood, urine, and stool metabolomes (short, medium, and long chain fatty acids, amino acids, carbohydrates, and bile acids); (2) items other than nutrients evaluated in the secondary endpoints and items evaluated by the diabetes treatment satisfaction questionnaire (DTSQ) [17]; (3) items other than physical examination evaluated in the secondary endpoints; (4) items other than gut microbiota evaluated in the secondary endpoints; (5) change in lipopolysaccharide-binding protein; (6) subgroup analysis by age, sex, etc. Harm outcomes will also be evaluated based on various laboratory abnormalities and adverse reactions to the medication.

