The primary endpoints will be evaluated using analysis of covariance. A two-sample t-test will be performed for between-group comparisons and a one-sample t-test will be performed for within-group comparisons. The secondary endpoints will be evaluated using a two-sample t-test or one-sample t-test. For data without a normal distribution, the log-transformation will be attempted; however, if it does not improve the distribution, Wilcoxon rank-sum test or Wilcoxon signed-rank will be performed. For the Bristol scale score, between-group comparisons will be performed using the Wilcoxon rank-sum test, and within-group comparisons will be performed using the Wilcoxon signed-rank test. For percentage endpoints, the χ-square test or Fisher’s direct probability test will be performed. For safety, a list of all adverse events will be prepared for each group in the safety analysis population; if necessary, comparisons between groups will be made using Fisher’s direct probability test.

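### The only Bristol score comparison the article lists spans constipation and diarrhoea patients, whose improvement runs in opposite directions, so it can mask a real effect on this exploratory endpoint

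*Protocol article*

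**What the plan says.** Under Outcomes, the first group of secondary endpoints is change and percent change from baseline to follow-up in a list that includes "GSRS subdomain scores, fecal properties/Bristol stool form scale, defecation frequency, blood test biomarkers". No restriction by symptom type is attached. Statistical methods for primary and secondary outcomes then names the tests for this score: "For the Bristol scale score, between-group comparisons will be performed using the Wilcoxon rank-sum test". Change inside each arm gets a signed-rank test. Neither sentence mentions a stratum or a recoding of direction.

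Under Eligibility criteria, patients are excluded for "having both ≥ 3 on the GSRS constipation subscale and > 4 on the Bristol stool scale" and for "having both ≥ 3 on the GSRS diarrhea subscale and < 4 on the Bristol stool scale". Patients with both symptoms are also excluded. Outcomes sets the normal range of the Bristol score at 3.5 to 4.5.

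The analyses by symptom type are listed in two places. Outcomes has "5) stratification of following items by baseline symptoms (constipation/diarrhea): GSRS total score, GSRS subdomain scores", and goes on to the proportion with normal fecal properties, defecation frequency, blood biomarkers and gut microbiota. Methods for additional analyses names the same items. The Bristol score and its change appear in neither list.

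**The concern.** The two exclusions put the two symptom types on opposite sides of 4 (or at 4), and normal is the band around 4. A treatment that normalises stool form therefore raises the score in constipation and lowers it in diarrhoea. An all-patient comparison of raw change sets these movements against each other. The signed-rank test within arm does the same.

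Percent change adds an asymmetry: a move from 2 to 4 is +100%, while an equal move from 6 to 4 is −33%.

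At stake is how the stool-form result is read. A null Bristol comparison could mean no effect, or two real effects that offset each other. A positive one would partly reflect which symptom type was more common.

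**Working it through.** **The plan's own figure.** The article sizes the trial on GSRS total score. With difference 0.244, SD 0.412, two-sided alpha 0.05 and power 0.80, n per arm = 2 × [0.412 × (1.960 + 0.842) / 0.244]² = 44.8, so 45. With 10% dropout, 45 / 0.9 = 50 per arm, 100 in all. This reproduces. It does not concern the Bristol score and supplies only the number per arm used below.

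**Inputs from the documents.** 45 evaluable per arm, two-sided 5% level, rank-sum test on change. Symptom type is a minimisation factor (Intervention description; Sequence generation), so the mix should be similar in both arms. That balances the arms but does nothing to stop offsetting within them.

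**Inputs assumed.** The documents give no constipation:diarrhoea mix, no expected Bristol effect and no SD of Bristol change. All three are varied.

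**Net shift.** With constipation share p and the same benefit b toward normal in both types, the all-patient mean difference is p × b − (1 − p) × b = (2p − 1) × b. For b = 0.7:
- p = 0.5: 0
- p = 0.6: 0.14
- p = 0.7: 0.28
- p = 0.8: 0.42
- p = 0.9: 0.56

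**Simulation, central case.** There were 4,000 trials per mix. Change was Normal(+0.7, 1) in treated constipation patients, Normal(−0.7, 1) in treated diarrhoea patients and Normal(0, 1) in controls.

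| Constipation share | Rank-sum on raw change, all patients |
|---|---|
| 50% | 2.9% |
| 60% | 6.8% |
| 70% | 19.3% |
| 80% | 44.1% (up to 48% on repetition) |
| 90% | 69.4% |

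With change signed toward normal, power was 88.7% to 89.5% whatever the mix (about 90% on repetition).

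**Other effect sizes.** A separate simulation used 3,000 trials per setting and SD 1.0. The last column is a rank test stratified by symptom type (van Elteren) on change signed toward normal.

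| Benefit | 50:50 | 60:40 | 70:30 | 80:20 | 90:10 | Signed, stratified |
|---|---|---|---|---|---|---|
| 0.6 | 3% | 6% | 15% | 34% | 56% | 77% to 79% |
| 0.8 | 2% | 8% | 22% | 57% | 81% | 95% to 96% |

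**Wider range.** With benefits of 0.5 to 0.9 and SD 0.8 to 1.3, the all-patient test has power of 1% to 5% at 50:50 and 9% to 40% at 70:30. The signed version has 41% to 99.9%, depending on effect and SD.

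**The case against.** Several points can fairly be made in the plan's defence.

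- **The article does not say the test is pooled.** It names a type of test and leaves detail to a separate analysis plan that is not shown. This stands as a limit on wording: the all-patient comparison is the only one this article lists, not necessarily the only one that will be run. But the article does fix the test and does enumerate the by-symptom items, twice, without the Bristol score. An analysis plan that followed it would carry the problem over.
- **A direction-free analysis already exists.** The proportion within 3.5 to 4.5 counts normalisation from either side and is listed by symptom type, as are the GSRS subdomain scores. This stands in part. The proportion misses improvement that stops short of the range. In the 0.7-point scenario its power was roughly 14% to 33%, depending on the assumed baseline.
- **The endpoint is exploratory.** This stands. Every endpoint other than the primary one has that status, and the GSRS total score is not touched.
- **The signed comparator is generous.** This also stands. It counts movement past normal as further improvement. Change in distance from 4, which penalises overshoot, had about 37% to 81% power depending on the assumed baseline. At its lower end, that is below the all-patient test at 80:20.

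A reader might infer that a real benefit will cancel out, or that the trial's stool-form result would be uninterpretable. The documents support neither. Full cancellation needs a balanced mix and equal benefits, and no mix is stated. A null Bristol result would also be read beside the stratified normal-range proportion. Nor do the documents rank the Bristol score above that proportion as a stool-form measure. Defecation frequency might seem to share the fault, but it is already listed by symptom type.

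**Conclusion.** The point holds as a cheap improvement to one exploratory secondary endpoint. As listed, the Bristol comparison mixes two populations for whom benefit has opposite signs, and it can mask a real effect. The loss is complete at a 50:50 mix with equal benefits and shrinks as one symptom type dominates. In the central case, power against the signed comparator's 89% to 90% is about 3% at 50:50 but 69% at 90:10.

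These sizes rest on an assumed benefit, an assumed SD, normally distributed change, equal benefit in both types and the same mix in each arm. The direction of the problem does not depend on the particular values. It follows from the eligibility rules and the normal range.

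**What to change.** Add Bristol score change to the symptom-stratified items under Outcomes and under Methods for additional analyses. Report the between-arm and within-arm comparisons separately for constipation and diarrhoea.

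If one overall result is wanted, replace the all-patient test of raw change with a rank test stratified by symptom type (van Elteren) on change signed so that positive means toward normal. Read it beside the proportion within 3.5 to 4.5, because signed change credits overshoot. Defecation frequency needs no change.

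The cost is wording, best settled before the data are fixed. The Bristol score and symptom type are already collected. The price is smaller numbers per stratum: with 22 constipation patients per arm (a 50:50 mix), power within that stratum was about 48% for a 0.6-point benefit and 72% for 0.8, at SD 1.0.

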#### Interim analyses

No interim analyses will be conducted in this study.

#### Methods for additional analyses (e.g., subgroup analyses)

Subgroup analyses of baseline symptoms (constipation/diarrhea), GSRS total score, GSRS subdomain scores, proportion of participants whose fecal properties are within the normal range, defecation frequency, blood test biomarkers, and gut microbiota will be performed.

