#### Sample size

In a sub-analysis of a previous study [15,18], BBG9-1 oral administration changed the total GSRS score by -0.441 ± 0.499. In the non-treatment period, the change in the total GSRS score was -0.197 ± 0.314. Based on these findings, assuming a difference of 0.244 ± 0.412 in the change in GSRS between the two groups in the study, we obtained an alpha error of 0.05, a power of 0.80, and a sample size ratio of 1:1; 45 cases per group would be needed to detect a significant between-group difference. Dropouts with a dropout rate of 10%, 50 cases in one group, and 100 cases in both groups have been set as the target number of cases for this study.

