### Statistical methods

#### Statistical methods for primary and secondary outcomes

Full analysis set (FAS) analysis will be performed for the primary and secondary endpoints. If necessary, per protocol set (PPS) analysis will be performed as a sensitivity analysis for the FAS analysis. In principle, the analysis should be performed at a two-sided significance level of 5%. The person responsible for the statistical analysis will prepare a separate statistical analysis plan that specifies the details of the statistical methods, including data handling. A statistical analysis plan will be prepared before the data are fixed. The primary endpoints will be treated as validation results, whereas the other endpoints will be treated as exploratory results.

The FAS will include the participants who are enrolled in the study and assigned to the study treatment. However, data on participants who violated the research protocol, such as enrolment without consent and registration outside the contract period, will be excluded. The PPS will include research participants who will be excluded from the FAS for the following reasons: violation of eligibility criteria, violation of exclusion criteria, violation of concomitant use of prohibited medications, and medication compliance rate > 120% or < 75%. The safety analysis set will include participants in whom research treatment has been initiated.

Summary statistics for the background data of study participants will be calculated for each group. Comparisons between groups will be made using the χ-square test or Fisher’s direct probability test for categorical variables and the two-sample t-test or Wilcoxon rank-sum test for continuous variables.

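### For the exploratory results by symptom type, the only tests the article names are run separately within each stratum, and none compares the treatment effect between constipation and diarrhea

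*Protocol article*

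**What the plan says.** In the protocol article, item (5) of the secondary endpoints (Outcomes) is "stratification of following items by baseline symptoms (constipation/diarrhea): GSRS total score, GSRS subdomain scores", followed by normal stool form, defecation frequency, blood biomarkers and gut microbiota. Under Statistical methods for primary and secondary outcomes, the rule is: "The secondary endpoints will be evaluated using a two-sample t-test or one-sample t-test". Log-transformation and then Wilcoxon tests are the fallback for non-normal data, Wilcoxon tests are set for the Bristol score, and χ-square or Fisher tests for percentages. Analysis of covariance is named for the primary endpoint only.

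Methods for additional analyses promises "Subgroup analyses of baseline symptoms (constipation/diarrhea), GSRS total score, GSRS subdomain scores" and the remaining items of the same list, and names no test. The statistical section also treats every endpoint except the primary as exploratory and leaves methodological detail to a separate statistical analysis plan. Symptom type is a minimization factor, and patients with both symptoms are excluded, so the two strata contain different patients.

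**The concern.** The trial enrols two opposite bowel complaints under one primary endpoint. Once the overall result is known, the natural next question is whether the probiotic helps in constipation, in diarrhea, or in both. That is a question about the difference between two treatment effects. The tests the article names answer other questions: whether the arms differ within one stratum, or whether one arm changed from baseline within one stratum.

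Two misleading patterns can follow. If one stratum is significant and the other is not, the result may be taken as a symptom-specific effect, although at this sample size that pattern is common when the effect is the same in both. And a significant within-arm change may be taken as benefit, although the article's own planning figures include an improvement without treatment.

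**Working it through.** **Inputs.** All come from the Sample size section. The planned effect is stated as "assuming a difference of 0.244 ± 0.412 in the change in GSRS between the two groups in the study". The other design values there are 80% power, equal allocation and 45 evaluable patients in each arm. Without treatment, a mean change of -0.197 (SD 0.314) is given. The test level is two-sided 5% (statistical methods section). The article does not give the symptom split, so that is an assumption, as are an equal true effect and an equal SD in both strata.

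**1. The plan's own figure.** n per arm = 2 × (1.960 + 0.842)² × 0.412² / 0.244² = 44.8, rounded up to 45. With 10% dropout, 45 / 0.9 = 50 per arm, 100 in total. Both figures reproduce. By the noncentral t distribution, power at 45 per arm is 79%.

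**2. Power in one stratum, even split.** 45 / 2 = 22.5 evaluable patients per arm per stratum. SE of the between-arm difference = 0.412 × √(2/22.5) = 0.123, and 0.244 / 0.123 = 1.99. Power is 49% by noncentral t (51% by the normal approximation).

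**3. Chance of a split result when the effect is identical.** The strata are independent, so with powers p and q:
- exactly one significant = p(1−q) + q(1−p)
- both = pq
- neither = (1−p)(1−q)

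| Assumed split | Power in each stratum | Exactly one | Both | Neither |
|---|---|---|---|---|
| 50:50 | 49% / 49% | 50% | 24% | 26% |
| 60:40 | 57% / 41% | 51% | 23% | 25% |
| 70:30 | 64% / 32% | 55% | 20% | 25% |
| 80:20 | 70% / 22% | 61% | 15% | 24% |
| 90:10 | 75% / 12% | 69% | 9% | 22% |

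At an even split, varying the SD from 0.35 to 0.50 moves the chance of exactly one significant result only between 46% and 50%. With all 50 patients per arm evaluable it is 50% at an even split.

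**4. One-sample test in untreated patients.** For 22.5 control patients in one stratum, the noncentrality is 0.197 / (0.314 / √22.5) = 2.98 on 21.5 degrees of freedom. The chance of significance is 81%, with no treatment given.

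**5. What an interaction estimate would deliver.** At an even split, SE = 0.412 × √(4/22.5) = 0.174. The 95% half-width is about 1.99 × 0.174 = 0.35. If the effects are equal, the test wrongly signals a difference 5% of the time. The difference detectable with 80% power is (1.960 + 0.842) × 0.174 = 0.49, twice the planned main effect. Power for a between-stratum difference of 0.244 is about 29%.

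**The case against.** The strongest reply is that the article is condensed, defers detail to an analysis plan that is not shown, and labels these endpoints exploratory. All of that is correct and limits the point in four ways.

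- A reader might infer that the trial has no test of whether the two effects differ. The documents do not support that. Only the article's silence can be shown; an interaction term may already be in the analysis plan.
- A reader might infer that efficacy by symptom will be decided by which stratum reaches significance. No section states such a rule.
- A reader might take the list in Methods for additional analyses as a plan to form subgroups on post-randomization outcomes. It repeats the outcome list of item (5) in the same order with the words on stratification dropped, and it never mentions follow-up values. It is loose drafting.
- The 50% figure rests on assumptions and concerns only the GSRS total score under an unadjusted t-test.

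It can also be said that the interaction test is too weak to settle the question. That is true, but it is equally a reason not to let separate p-values appear to settle it.

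What remains is that the article does choose a family of tests for secondary endpoints, item (5) is one of them, and no member of that family compares the strata. The exploratory label limits the strength of any claim; it does not turn two separate p-values into a comparison.

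**Conclusion.** The point holds as a limited, inexpensive improvement. For the exploratory symptom-stratified endpoints, the tests the article names are separate unadjusted between-arm tests and within-arm tests, and none estimates the difference in effect between constipation and diarrhea. If the planning values apply equally in both strata, significance in exactly one stratum is the most likely single pattern under an identical benefit: about 50% at an even split, rising to 61% at 80:20 and 69% at 90:10. Within-arm significance says even less, since untreated patients in one stratum would reach it about 81% of the time if the non-treatment change used for planning applies to them. The confirmatory analysis of the primary endpoint is not affected.

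**What to change.** For GSRS scores and the other continuous outcomes, estimate the effect by symptom from one model containing arm, symptom type, their interaction and the baseline value of the outcome. Report the between-arm estimate in each stratum with a 95% CI, and the interaction estimate with its CI. State that neither significance in one stratum only nor a within-arm change shows a symptom-specific benefit. If the analysis plan already has such a model, a matching sentence in the protocol is enough.

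As a minor editorial matter, reword the list in Methods for additional analyses to match item (5): the listed outcomes, stratified by baseline symptom.

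The cost is wording and one added model term. Symptom type is already an allocation factor, and baseline values are already collected. The price is precision: an interaction CI of about ±0.35 on the GSRS total score, with 80% power only for a between-stratum difference near 0.49, so some symptom-specific claims would have to be given up.
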